## Abstract

**Background:**

Treatment of the older diabetic individual comprises a therapeutic challenge. Currently little scientific evidence exists depicting the best approach to type 2 diabetes treatment in this growing sub-population of patients. The purpose of this study is to assess the effects of a modified plant-based Mediterranean diet (“vegeterranean” diet), circuit resistance training (CRT) and empagliflozin, separately or in combination, on body composition and physical function in older subjects with type 2 diabetes. The rationale for this study is to assess three interventions associated with a negative energy/caloric balance (increased caloric use in exercise, caloric restriction in the “vegeterranean” diet and caloric wasting by glycosuria with empagliflozin), their interaction and effect on body composition and physical function.

**Methods:**

One hundred and twenty men and women ≥65 years of age with type 2 diabetes, and low levels of physical activity will be randomized (1:1:1 manner, gender stratified) for 10 weeks to one of 3 parallel arms: CRT consisting of 3 home sessions/week; ad-libitum plant-based Mediterranean diet (limited consumption of eggs, dairy and fish, avoidance of red meat and poultry) or empagliflozin 10 mg/day. After 10 weeks CRT will be added to the empagliflozin and diet arms for an additional 10 weeks. Allocation concealment and blinding of primary outcome assessors will be implemented. Efficacy will be determined by assessment of lean body mass, body weight, frailty and functional status, sarcopenia, HbA1c and quality of life questionnaires. Safety will be evaluated by routine monitoring of adverse events. This study was approved by the Tel-Aviv Sourasky Medical Center Institutional Review Board.

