### Visit 1- screening

All potential eligible subjects will be invited for a screening Visit 1, during which the following information would be obtained:
Informed consent.Physician interview and physical examination.A questionnaire adapted from the national Israeli health and nutrition survey (MABAT) for the older people which includes demographic details, health status, lifestyle as well as descriptive details addressing the functional and physical state.A meeting with the research assistance (AL) (blinded during all study) to assess adherence to the Med-diet, using the PrediMed screener which was recently adopted to Israel.A meeting with the study’s physiologist (OK) comprised of a short interview and frailty and functional assessments.

Screening information from all subjects will be documented and kept in a screening log. Comparisons of baseline characteristics of the included vs. the excluded subjects will be performed at the end of the trial (age, gender, etc.).

### Visit 2- day 1

Subjects that were confirmed as eligible at the end of Visit 1 will be considered as “included subjects”. During Visit 2, subjects will be assigned a 5-digit number (their 5 first ID number’s digits) and the following information will be collected:
Following overnight fasting (12 h) patients will undergo: a) resting metabolic rate (RMR); b) Anthropometric assessment (then food is allowed); c) Fasting blood draw for routine glucose and hormonal profile; d) Blood Pressure (BP) (diastolic and systolic) and pulse measurements; e) eye examination.

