##### Blinding

As mentioned we will use allocation concealment, such that at baseline all outcome assessors will be blinded to allocation. At follow up outcome assessors that will be blinded to the participants allocation will include: laboratory technicians (performing blood analysis); research assistant (AL) (in charge of nutritional analysis and the Med-diet questionnaire); ophthalmologist (for eye examination); endocrinologist (YM) (analyzing the 24–hour ambulatory blood pressure monitoring [ABPM]); another researcher (AD) (analyzing the quality of life questionnaires). The study physician (RE), nutritionist (AB), physiologist (OK) and physical instructor (AR) will not be blinded due to their role of instructing the patients on the intervention as well as collecting the following outcomes: body composition (automatic analysis but measured by AR); food intake and RMR (AB) and physical performance tests (OK).

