### Follow up visits

Subjects will attend the IEMH at TASMC at the following intervals: screening Visit 1, Visit 2- Day 1- baseline day (allocation will be exposed at the end of baseline day; subjects allocated to SGLT-2 arm will meet the physician (RE) for instructions on the drug), Visit 3 Week 0- familiarization of protocol – meeting with the dietitian (AB) for V-Med arm only. Subjects allocated to the CRT arm will meet the physiologist (OK) or a physical instructor (AR) at their homes for familiarization. From familiarization day the 20-week count of the study period will start, and subjects will have an additional five “on site visits” at Week 1 (V-Med arm only; CRT – another visit at home after 1 week from beginning), Week 6 (V-Med arm only), Week 10 (all arms; CRT arm – end of study), Week 16 (V-Med arm only) and Week 20 (SGLTT-2 and V-Med arms) (Table 1).

**Table 1 Tab1:** Study flow chart

	Screening	Baseline day (W0–1)^e^	Familiarization of protocol^b^ (W0–2)	After 1 week (W1)	After 6 weeks (W6)	After 10 weeks^c^ (W10)	After 16 weeks (W16)	After 20 weeks (W20)
On site visit number	1	2	3	4	5	6	7	8
Informed consent	X							
Eligibility criteria form	X							
Medical discharge and list of drugs from primary physician + physical activity confirmation letter	X							
Blood examinations from last 3 months (for eligibility)	X							
Physical examination for vital signs by study physician	X					X		X
Screening blood and urine tests (biochemistry and endocrinology): a) Urine microalbumin, sodium, creatinine, free cortisol) b) TSH, FT4 c) 25 OH vitamin D	X							
Demographic details, questions on health status, lifestyle using MABAT questionnaire	X							
Functional and physical activity questionnaires	X							
Food frequency questionnaire	X							
Guidance about diabetes diary	X							
Drug guidance for drug arm only		X						
Dietary guidance for diet arm only			X	X	X		X	
CRT guidance for CRT arm only			X	X				
CRT guidance for drug and diet arms						X		
Height		X						
Body weight		X				X		X
Body circumferences		X				X		X
Body fat %, lean and muscle mass assessments using BIA method		X				X		X
Resting blood pressure		X				X		X
Resting energy expenditure		X				X		X
24 h blood pressure monitoring		X				X		X
Fasting plasma glucose and HbA1C		X				X		X
Testosterone (T) and bioavailable T		X				X		X
HOMA- Insulin X glucose/23.5		X				X		X
LH, FSH, Estradiol		X				X		X
Diabetes diary (self-monitoring glucose levels, change in drugs)		X				X		X

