### Main ascertainment of response variables

#### Anthropometric and sarcopenia

Anthropometric measurements will be obtained following a uniform protocol. Height, weight, waist and hip circumference will be measured twice. LBM, skeletal muscle mass (SMM), fat mass (FM) and % fat will be evaluated by the direct segmental multi-frequency bioelectrical impendence analysis (BIA) technique method using the ‘In-Body 770 body composition analyzer’. The In-Body 770 is a valid tool for the assessments of total body and segmental body composition [40]. Sarcopenia will be assessed in line with the consensus definition offered elsewhere [41] using three parameters: a) low skeletal muscle mass; b) low muscle strength; c) low physical performance [41]. Pre-sarcopenia will be defined as low skeletal muscle mass but normal strength and physical performance, whereas sarcopenia will be defined as having both low muscle mass with either low muscle strength or low physical performance. Severe sarcopenia will be determined by the presence of all 3 criteria (low muscle mass + strength + low performance). Skeletal muscle mass will be obtained by the In-Body (770) body composition analyzer. Shortly, the skeletal muscle index (SMI = skeletal muscle mass/body mass × 100) will be compared to gender-specific reference norms of young adults (aged 18–39 years). Sarcopenia will be defined as any value < 10.76 kg/m^2^ for men and < 6.76 kg/m^2^ for women [42]. Low muscle strength and low physical performance will be assessed using grip strength and gait speed test as described in the following paragraph on frailty.

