##### Baseline comparisons

To test differences in continuous variables between the study groups the one-way analysis of variance (ANOVA) test will be performed (or Kruskal–Wallis one-way analysis of variance when normal distribution is rejected). For comparison of dichotomous or categorical variables the Chi square test will be performed.

The primary endpoints (% change in LBM and change in weight) will be analyzed using the analysis of covariance (ANCOVA) after 10 weeks and after 20 weeks (for diet and drug arms only) including several factors and covariates. Table 2 indicates the list of covariates and factors. Table 3 indicates the different outcomes and appropriate statistical method.

**Table 2 Tab2:** List of potential covariates and factors (partial list)

Factor or covariate	Type	Defined as
Treatment	Factor	SGLT2 inhibitor, diet, CRT
GLP1 agonists	Factor	Yes, no
Baseline body weight/ BMI	Covariate	–
HbA1c (%)	Covariate	–
Caloric consumption (Kcal)	Covariate	–
Resting metabolic rate (Kcal)	Covariate	–
Body fat %	Covariate	–
Strength (kg)	Covariate	–
Frailty or sarcopenia status	Factor	Frail or sarcopenic, pre-frail or pre sarcopenic and robust

*Abbreviations*: *BMI* Body Mass Index, *CRT* Circuit Resistance Training, *GLP-1* Glucagon-Like Peptide-1, *HbA1c* Hemoglobin A1C

**Table 3 Tab3:** The different outcomes and appropriate statistical method (partial list)

	Endpoint type	Statistical method
Primary outcome		
Change in body weight (%) from baseline to 10 weeks or to 20 weeks	Continuous	ANCOVA
Change in % lean body mass from baseline to 10 weeks or to 20 weeks	Continuous	ANCOVA
Proportion of participants having lost ≥2.5% at week 10 and 20	Binary	Logistic regression
Secondary outcomes		
Change in waist circumference from baseline to 10 weeks or to 20 weeks	Continuous	ANCOVA
Change in FPG and HB1Ac from baseline to 10 weeks or to 20 weeks	Continuous	ANCOVA
Change in sarcopenia and frailty status (improved vs. not improved; change from one level to the other) at week 10 and 20	Binary	Logistic regression
Change in strength and other functional abilities from baseline to 10 weeks or to 20 weeks	Continuous	ANCOVA
Change in systolic blood pressure from baseline to 10 weeks or to 20 weeks	Continuous	ANCOVA
Change in quality of life (improved vs. not improved; change from one level to the other) at week 10 and 20	Binary	Logistic regression

*Abbreviations*: *ANCOVA* Analysis of Covariance, *FPG* Fasting Plasma Glucose, *HbA1c* Hemoglobin A1C

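### The abstract promises blinded primary outcome assessors, but the Blinding section supports this only at baseline: at weeks 10 and 20 lean mass is measured unblinded, and nobody is named for weight

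*Protocol article*

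**What the plan says.** The Methods paragraph of the abstract states without qualification: "Allocation concealment and blinding of primary outcome assessors will be implemented".

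The Blinding section separates two time points. At baseline, allocation concealment keeps every assessor blind. For later visits it gives a list: "At follow up outcome assessors that will be blinded to the participants allocation will include: laboratory technicians", followed by the staff responsible for nutritional analysis and the Mediterranean-diet score, the eye examination, ambulatory blood pressure and quality of life. It then says that the study physician, nutritionist, physiologist and physical instructor "will not be blinded due to their role of instructing the patients on the intervention as well as collecting the following outcomes: body composition". Body composition is assigned to the physical instructor, with a note that its analysis is automatic. Food intake and resting metabolic rate go to the nutritionist, "and physical performance tests" to the physiologist.

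The primary endpoints are named under Baseline comparisons: "The primary endpoints (% change in LBM and change in weight) will be analyzed using the analysis of covariance (ANCOVA". Table 3 adds the proportion of participants losing at least 2.5%. The measurement method is under Anthropometric and sarcopenia: "LBM, skeletal muscle mass (SMM), fat mass (FM) and % fat will be evaluated by the direct segmental multi-frequency bioelectrical impendence analysis (BIA".

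**The concern.** A reader who sees only the abstract will credit the trial with masked measurement of its primary outcomes. The body of the article assigns at least one of those outcomes, LBM, to someone who knows the arm and coaches participants. An abstract should not claim a protection that the methods withdraw.

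What is at stake differs by outcome. An impedance device leaves the operator little room to influence the reading. Sit-to-stand, timed up-and-go, two-minute walk, grip and knee extension depend on effort, encouragement and, in part, hand timing. Hypothesis 2, listed under the primary aims, predicts that function improves most with CRT at week 10, and the tester is one of the people who teach CRT. An unconscious difference in encouragement would plausibly run in the direction of that hypothesis.

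**Working it through.** No arithmetic applies, because the point is whether two statements in the same article agree. The sections are set side by side.

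**1. What the abstract's claim covers.** It concerns assessors of primary outcomes and is not limited to baseline. The primary outcomes in Table 3 are changes from baseline to week 10 or 20, or proportions at those weeks. The claim therefore has to hold at follow-up.

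**2. Who assesses each outcome at follow-up.**

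| Outcome | Status | Assessor at weeks 10 and 20 | Blinded? |
|---|---|---|---|
| % change in LBM (bioimpedance) | Primary (Table 3) | Physical instructor | No, stated in Blinding |
| % change in body weight; loss of at least 2.5% (taken here to mean body weight) | Primary (Table 3) | Not named | Not stated |
| Physical performance tests | Hypothesis 2 under the primary aims; secondary in Table 3 | Physiologist | No, stated in Blinding |
| Laboratory, nutrition and Mediterranean-diet score, eye examination, ambulatory blood pressure, quality of life | None is a primary outcome in Table 3 | Listed staff | Yes |

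No row with a primary outcome has a blinded assessor. For LBM the abstract is contradicted. For weight it is unsupported.

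**3. Weight also enters the LBM endpoint.** Definition of main outcomes builds relative lean mass change from lean mass as a proportion of body weight. The unanswered question of who measures weight therefore touches every primary outcome.

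**4. Do the testers deliver the intervention?** Yes. Under Follow up visits, "Subjects allocated to the CRT arm will meet the physiologist" or a physical instructor at home for familiarization. The Blinding section gives this instructing role as the reason why these staff are not masked.

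**5. Which comparisons are exposed.** At week 10 the CRT arm is compared with two arms that have not yet started CRT, so a tester who is also the CRT trainer could favour one side. Footnote c of Table 1 ends the CRT arm at week 10 and adds CRT to the other two. The week-20 comparison is therefore between two arms that both receive CRT. The tester still knows the arm and Hypothesis 2 is still directional, but the trainer has no evident reason to favour either arm.

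**6. What does not count as evidence.** The entry for Visit 1, "A meeting with the study’s physiologist", gives the physiologist the frailty and functional assessments at screening. Randomization comes at the end of Visit 2, so that meeting takes place before any allocation is known and says nothing about blinding at follow-up.

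**The case against.** The best defence is that the article is candid everywhere except in one sentence. Trial design calls the study open label, Data confidentiality calls it unblinded, and the Blinding section says who is unmasked, why, and for which outcomes. Unmasked testing in a single-center exploratory lifestyle trial is a disclosed limitation. This stands: the provable fault is the abstract's claim, and only a reader of the abstract alone is misled. It does not remove the fault, because an open-label trial can have blinded assessors and the abstract says that this one does.

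It can also be said that the abstract is true at baseline and that impedance output is automatic. Both are correct. The first does not cover endpoints measured at weeks 10 and 20. The second reduces the bias in LBM but does not make the instructor blind.

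Three stronger readings are tempting, and the documents do not support them:

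- **That all primary outcomes are measured unblinded.** No section says who weighs participants. For weight, the text shows only that no blinded assessor is named.
- **That the false-positive rate is inflated by a known amount.** Suppose a bias of 0.2 to 0.3 SD towards CRT, 40 per arm, no true effect and an unadjusted two-sample t-test at 5%. The noncentrality is 0.2 × √(40/2) = 0.89 to 0.3 × √(40/2) = 1.34, and the test would reject in about 14% to 26% of trials. Nothing in the article supports a bias of that size. The plan uses ANCOVA with Benjamini-Hochberg adjustment, and the affected outcomes are secondary in Table 3. These figures illustrate an assumption and are not the trial's error rate.
- **That bias favours CRT throughout.** As step 5 of the working shows, that argument applies to week 10 and not to week 20.

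**Conclusion.** The point holds as an internal contradiction. The abstract's statement is wrong for LBM at weeks 10 and 20 and unsupported for weight; it is right only for baseline. The conclusion rests on the text alone and needs no assumption about effect sizes.

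The likely effect on the LBM result is limited by the automatic analysis. The physical performance tests are more exposed, chiefly in the week-10 comparison of CRT with the other arms. The size of that bias cannot be derived from the documents, and its direction is a plausible inference, not something they show.

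**What to change.** **Required.**

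- Reword the abstract to say that assessors are blinded at baseline, and that at follow-up only the laboratory, nutrition and Mediterranean-diet score, eye, ambulatory blood pressure and quality-of-life assessors are blinded.
- State that LBM and the functional tests are assessed unblinded at follow-up.
- State who measures body weight and whether that person is blinded.
- In reporting, treat the week-10 functional results as open to assessor bias.

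This costs a few sentences and changes no procedure.

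**Preferred where feasible.** Have existing blinded staff run the functional tests and the impedance and weight measurements at weeks 10 and 20 from a fixed script, with participants asked not to disclose their arm. Visit 1 describes a research assistant who stays blinded for the whole study, and Table 1 already schedules the Mediterranean-diet assessment at both weeks. The cost is brief training and a risk of unmasking. Participants may reveal their arm, and diet records may do so too, since the diet arm avoids red meat and poultry. The article does not show whether that assistant is trained or available for these tests, so this step depends on a local check. The corrected wording should be adopted unless that check succeeds, and then adjusted to whatever is put in place.

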**Discussion:**

The combination and comparison of these diverse interventions to metabolic control may lead to better understanding of their mechanism of action with potential clinical implications in older individuals. Also, this study will provide evidence of the effectiveness of these interventions on delaying the progression from diabetes to sarcopenia and/or frailty.

**Trial registration:**

ClinicalTrials.gov PRS: NCT03560375. Last registration date (last update): 06/06/2018. The trial was a-priori registered before actual recruitment of subjects.

**Electronic supplementary material:**

The online version of this article (10.1186/s12877-019-1219-7) contains supplementary material, which is available to authorized users.

## Background

Longevity has been steadily increasing over the past several decades. Life expectancy in 65-year old Israeli adults is ~ 20 years, leaving an ever expanding time window for the evolution of loss of health and function [1]. In western countries, the proportion of people over age 60 is increasing faster than any other group [2]. Diabetes rates (mainly type 2 diabetes mellitus -T2DM) are increasing in general and in older adults [4]. In the past the older population was characterized by low body weight and malnutrition in contrast to the present in which rates of obesity, metabolic syndrome and T2DM are increasing [3, 4]. Due to its chronic nature, T2DM presents a challenge to both patients and healthcare systems in maintaining adherence to treatment and accompanying lifestyle changes [5, 6].The risk for T2DM related complications is age related and is accompanied by functional limitation and comorbidities [7, 8]. One morbidity associated with diabetes in the older population is sarcopenia [9] – a phenomenon of age-related loss of skeletal muscle mass, strength and function. The decreased muscle mass is associated with loss of strength, increased likelihood of falls, and loss of autonomy [10].

Whereas weight reduction and physical activity are cornerstones of T2DM treatment and are likewise recommended as first-line treatment in adults [8], the older subpopulation is underrepresented in clinical trials [4]. Numerous diet regimens have been shown to improve T2DM control in relatively short clinical trials including the Mediterranean diet (Med-diet) [11], vegetarian / vegan [12, 13] and low-carb diets [12, 14, 15]. However, in older individuals, low-carb diets resulted in contradicting results [14, 15]; a meta-analysis of 10 randomized controlled trials (RCTs) comprising 1376 participants (age range 54–63 yrs.) showed that in the first year of intervention (3 or 6 months), a low carbohydrate diet (< 45% of total caloric consumption) was followed by a 0.34% lower HbA1c compared with a high carbohydrate diet (45–60% of total caloric consumption). However, at 1 year or later, HbA1c was similar in the two groups with higher dropout rates in the low carbohydrate diet groups [14]. Med-diet with a vegetarian pattern (the “vegeterranean” diet- V-Med diet) has a higher portion of carbohydrates when compared to low-carb diets, accompanied with high levels of fat (mainly unsaturated). To the best of our knowledge the V-Med diet has never been studied in older patients with T2DM.

In addition to diet, physical activity (PA) is an integral part of T2DM therapy, as it is associated with a lower risk of cardiovascular disease and mortality [16]. However, adherence to exercise in older adults is low and studies in older adults performing unsupervised physical activity are scarce and have shown limited improvement in performance when compared to fully supervised programs [17, 18]. The cost of supervised training programs limits their widespread use and results in a need to develop more achievable evidence-based “shorter duration” home-training regimens [17] in older people with T2DM.

In addition to low adherence to PA, insulin resistance, a key pathogenic process in T2DM and a common condition in older individuals, is associated with “anabolic resistance”, which interferes with any attempted increase or preservation of skeletal muscle mass [19]. Anabolic resistance is associated with sarcopenic obesity and frailty [20] and requires careful management of weight reduction while performing PA [21].

Recently, we have shown that circuit resistance training (CRT) is effective in increasing muscle mass and especially muscular strength in older adults with diverse health conditions [22]. CRT performed with minimal supervision (performed in the patient’s home) was never studied in a Randomized Controlled Trial (RCT) in healthy or diabetic older individuals.

Empagliflozin is a new antihyperglycemic medication that induces glycosuria via inhibition of the renal sodium-glucose transporter-2 (SGLT-2) [23–25]. Independent of its anti-hyperglycemic effect, empagliflozin is cardio-protective in diabetic patients with pre-existing cardiovascular disease [26, 27]. Treatment with empagliflozin and other SGLT-2 inhibitors results in weight loss (through urinary caloric loss) and potential compensatory hyperphagia without a significant change in resting metabolic rate (RMR) [24, 25, 28, 29].

In this study we aim to compare the effect of a V-Med diet, CRT and empagliflozin separately or in combination on metabolic and anthropometric parameters in older subjects with T2DM. Both SGLT2 inhibitors and exercise lead to increased caloric expenditure and compensatory hyperphagia; SGLT2 inhibitors and diet lead to weight loss and all three interventions reduce insulin resistance and lower circulating insulin levels [30, 31]. Therefore, the combination of and comparison among these diverse approaches to metabolic control may lead to better understanding of their mechanism of action with potential clinical implications in older individuals.

In conclusion, treatment of the older diabetic individual comprises a therapeutic challenge. Currently little scientific evidence exists depicting the best approach to T2DM treatment in this growing sub-population of patients. In this study we aim to better quantify the short-term effects of diet, physical activity and drug therapy, alone or in combination, on metabolic and anthropometric parameters as well as on physical function in older individuals with T2DM.

